## Methods

### Design

The FORTRESS trial is a multi-site hybrid type II stepped wedge, cluster randomised trial to be conducted over three years (see Fig. 1). This study protocol is reported in accordance to the Standard Protocol Items: Recommendations for Intervention Trials (SPIRIT) checklist available as supplementary file. The hybrid type II trial approach [20] allows testing of the implementation strategy (Implementation Facilitation [21]) and testing the outcomes of the intervention (screening for frailty and use of appropriate interventions).

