### Intervention

Patients admitted to the wards taking part in this study are screened for eligibility. Baseline frailty is measured using the FRAIL scale [8] and a score of 3 and above indicates frailty. If the person has been admitted to a ward during the control phase of the research study, they will receive usual care as provided by the ward staff and their general practitioner and other health service providers. Participants admitted to the ward during the intervention phase will receive an individualised intervention designed to treat the identified components of frailty, along with the community implementation visit(s), telephone calls, and support from their general practitioner (GP) once discharged. Additional file 1 outlines the TIDier framework [26] describing the FORTRESS intervention. Intervention is divided into two phases:

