### Statistical analysis

The primary analysis will compare length of stay in hospital at readmission after the index hospital admission during 12 months of follow up between intervention and control conditions, using generalised linear mixed models with a negative binomial distribution, accounting for clustering by wards and adjusting for credible confounders to further control baseline imbalance. The approach will be intention to treat.

Secondary analyses will compare time to event of readmission between intervention and control conditions using survival analysis, and frailty status, quality of life outcomes and readmission rates using linear mixed models, accounting for clustering by ward and adjusting for credible confounders.

Covariables to be considered in these analyses will include age, sex, degree of frailty at index admission, number of hospitalisations in the preceding 12 months, cognition (MMSE score), and primary admission diagnosis for the index admission and for readmissions. SAS and R statistical software will be used for analysis.

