### Randomisation procedure

Transition to the intervention phase will be randomised by ward with stratification by site and using minimisation with a random component to optimise baseline and sequential balance. To do this the minimisation algorithm will use anticipated ward characteristics including the type of ward, typical length of stay, high or low tendency to discharge to a day rehabilitation ward rather than home and, where possible, typical readmission rates at that ward.

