### Economic analysis

The total cost of delivering the intervention will be assessed, and cost-effectiveness analyses will be conducted, according to the principles for conducting economic evaluation alongside stepped wedge trials [30]. The economic evaluation will take the perspective of the health care funder and will include analyses for health outcomes measured in terms of the main clinical outcomes, including cost per extra person avoiding readmission, cost per extra person avoiding frailty, and cost per quality adjusted life years (QALY) gained based on the EQ-5D-5L. The study will collect data on the cost to deliver the intervention (including staff costs, training, capital costs and consumables), and inpatient hospital admissions, based on DRG-related costs. Using the mean costs in each trial arm, and the mean health outcomes in each arm, the incremental cost per extra person avoiding frailty, per extra person avoiding re-admission and per QALY gained of the intervention group compared with control group will be calculated; results will be plotted on a cost-effectiveness plane. Bootstrapping will be used to estimate a distribution around costs and health outcomes, and to calculate the confidence intervals around the incremental cost-effectiveness ratios. One-way sensitivity analysis will be conducted around key variables. A probabilistic sensitivity analysis will be conducted to estimate the joint uncertainty in all parameters, and a cost-effectiveness acceptability curve (CEAC) will be plotted.

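### The economic evaluation writes out a contrast of arm means and states no calendar-period or ward adjustment, although condition in this stepped wedge depends on when a ward crosses over

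*Protocol article*

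**What the plan says.** The Design section describes the trial: "The FORTRESS trial is a multi-site hybrid type II stepped wedge, cluster randomised trial to be conducted over three years". Under Randomisation procedure, "Transition to the intervention phase will be randomised by ward with stratification by site". Under Intervention, a participant's condition follows from the ward's phase at admission: "If the person has been admitted to a ward during the control phase of the research study, they will receive usual care".

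The Economic analysis section commits the cost-effectiveness work to a design-specific standard, "according to the principles for conducting economic evaluation alongside stepped wedge trials [30" (a citation whose content is not available here). It then sets out the calculation. The incremental costs per person avoiding frailty, per person avoiding readmission and per QALY are obtained "Using the mean costs in each trial arm, and the mean health outcomes in each arm". On uncertainty it says: "Bootstrapping will be used to estimate a distribution around costs and health outcomes, and to calculate the confidence intervals around the incremental cost-effectiveness ratios". Calendar period, ward, baseline utility and the unit of resampling are not mentioned.

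The Statistical analysis section, in the same condensed article, describes the primary clinical model as "accounting for clustering by wards and adjusting for credible confounders to further control baseline imbalance", and says much the same for the secondary outcomes. It names no calendar-period term either.

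**The concern.** A difference in arm means is the standard estimator for a parallel trial. Here each ward supplies control participants first and intervention participants later. Pooled means by condition therefore compare an earlier period with a later one, and a mixture of wards weighted towards late crossers with one weighted towards early crossers. The Randomisation procedure section itself treats wards as differing in type, typical length of stay, discharge pattern and readmission rate, all of which plausibly bear on cost.

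Cost-effectiveness is a stated aim, and the Discussion hopes to show that savings on readmissions outweigh the cost of delivery. The point estimate, the intervals and the acceptability curve all start from this calculation. Inpatient costs are DRG-based and data collection runs from December 2020 to December 2023, so a change over those years in admission practice, or in prices if they are not held constant, would be read as an effect of the intervention.

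**Working it through.** The plan states no numerical result for the economic analysis, so there is no figure of its own to reproduce. The check asks how far the two conditions differ in time and ward mix when participants are simply pooled.

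**Inputs from the protocol article.** Six wards, 732 participants, recruitment over 16 months, a target of 35 versus 50 days (difference 15), and a design effect of 1.75 for ward clustering (all under Sample size).

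**Assumptions.** Fig. 1 is not shown, so I take S equal steps with 6/S wards crossing at each, S + 1 equal periods, an all-control first period and an all-intervention last period, and equal recruitment in every ward-period.

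**1. Gap in calendar time.** The midpoint of period p (p = 0, …, S) is (p + 0.5) × 16/(S + 1) months. Averaging over control cells and over intervention cells gives:

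| Steps | Control mean (months) | Intervention mean (months) | Gap (months) | Gap/12 |
|---|---|---|---|---|
| 6 | 4.95 | 11.05 | 6.1 | 0.51 |
| 3 | 4.67 | 11.33 | 6.7 | 0.56 |
| 2 | 4.44 | 11.56 | 7.1 | 0.59 |

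The last column is the share of a linear annual trend that enters a contrast of pooled means. The gap scales in proportion to the recruitment window.

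**2. What a trend would do.** The size of any trend is unknown. As an illustration on 50 days, shift = 50 × annual trend × gap/12:

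- 5% a year: 1.3 to 1.5 days, or 8 to 10% of the 15-day target
- 10% a year: 2.5 to 3.0 days, or 17 to 20%
- 20% a year: 5.1 to 5.9 days, or 34 to 40%

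The direction depends on the direction of the trend.

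**3. Ward mix.** With six steps each condition has 6 + 5 + 4 + 3 + 2 + 1 = 21 ward-periods. The first ward to cross supplies 6/21 = 29% of intervention participants and 1/21 = 5% of controls. For the last ward these shares are reversed.

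**4. Does the design effect of 1.75 show that intervals would be far too narrow?** Suppose individuals were resampled. The simple calculation is 1/√1.75 = 0.756, that is, standard errors 24% too small and coverage 2Φ(1.96 × 0.756) − 1 = 86% for a nominal 95% interval. That treats wards as nested within arms. Here each ward contributes to both conditions. Take m = 732/6 = 122 per ward and assume 1.75 = 1 + (m − 1) × ICC, so ICC = 0.75/121 = 0.0062. Let aᵢ and bᵢ be ward i's shares of the intervention and control participants, with 366 in each condition. Relative to independence, the variance of the pooled contrast is

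(1 − ICC) + ICC × Σ(aᵢ − bᵢ)² / (2/366).

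- Six steps: Σ(aᵢ − bᵢ)² = (25 + 9 + 1 + 1 + 9 + 25)/21² = 0.159, inflation 1.17, coverage 93%
- Three steps: 16/12² = 0.111, inflation 1.12, coverage 94%
- Two steps: 6/9² = 0.074, inflation 1.08, coverage 94%

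On these assumptions the understatement of uncertainty is modest. The main exposure is bias from calendar time and ward mix.

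**5. Price of adjustment in precision.** The pooled condition indicator has variance 0.25. After fixed ward and period effects are removed, with six steps, 0.25 − 0.0595 (between wards) − 0.1111 (between periods) = 0.0794 remains. For the same residual variance the standard error grows by √(0.25/0.0794) = 1.77. For three steps: 0.25 − 0.0417 − 0.1389 = 0.0694, factor 1.90. For two steps: 0.25 − 0.0278 − 0.1667 = 0.0556, factor 2.12.

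**The case against.** The strongest reply is that the section opens by adopting stepped wedge principles, and that this governs what follows. Arm means is ordinary wording for an incremental ratio and is compatible with model-adjusted means. Covariates, price year and bootstrap unit usually belong in a health-economic plan, which is not shown. Minimisation on ward characteristics also gives some protection against uneven ward mix.

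Much of this stands. A reader might infer that the plan uses raw means and ignores ward clustering. The text supports neither statement: it does not call the means unadjusted, does not say that individuals are resampled, and does not say that admissions are priced at different years. A reader might also infer 86% coverage from the 1.75. That does not follow: it supposes individual resampling, carries a factor given for readmission days over to costs and QALYs, and overlooks that ward effects partly cancel when the same wards supply both phases. If the 1.75 was derived in some other way, the inflation could be larger than the 1.08 to 1.17 found above. The article does not say.

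What the reply does not remove is that the one estimator written out does not reflect the design principle cited beside it. An analyst who followed the sentence would compute simple arm means. The clinical analysis paragraph, equally condensed, found room for ward clustering and confounder adjustment. Minimisation addresses balance between wards, not calendar time.

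**Conclusion.** The point holds as a mismatch between the cited stepped wedge principles and the calculation written out. Followed literally, that calculation mixes the intervention effect with calendar time and ward mix. The gap of about 6 to 7 months rests on equal steps and even recruitment over 16 months. The resulting bias cannot be sized without knowing the trend, and the 5 to 20% figures are illustrations only. No claim is made that the intervals will be seriously too narrow, nor that the analysis as finally run will be unadjusted. If a full economic plan already specifies adjusted increments, one clarifying sentence settles the matter. Otherwise the change is worth making before analysis, because it is cheap and cost-effectiveness is a main aim.

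**What to change.** Replace the arm-means sentence in the Economic analysis section so that it states the following.

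- Incremental cost, incremental QALYs, and the differences in persons readmitted and persons frail come from regression models with explicit calendar-period and ward terms, plus baseline EQ-5D-5L in the QALY model. List the terms in this section. A reference to the primary model would not be enough, because the Statistical analysis section names no period term. If ward is a fixed effect, no separate site term is needed, since wards lie within sites.
- All admissions are valued at one reference price year.
- The bootstrap respects wards: for example, resample participants within ward and period, refit the adjusted models in each replicate, and build the intervals and acceptability curve from those replicates. Add a ward-level sensitivity analysis, and acknowledge that six wards make it imprecise.

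The cost is wording and a little more programming on data already to be collected. Intervals will probably be wider: on the assumed layouts, standard errors grow by a factor of about 1.8 to 2.1 if the residual variance is unchanged. The narrower interval from pooled means would belong to a contrast that period and ward mix may bias.

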## Discussion

Frailty is associated with poorer outcomes for individuals and prevalence is likely to increase due to an ageing population. There is evidence that intervention can effectively reverse frailty and Asia Pacific Guidelines recommend screening and multidisciplinary intervention [16, 22, 23]. This study investigates the efficacy of implementing frailty guidelines for hospitalised older adults and explores the process of implementation in this setting. The results will provide important information which can be used by health care policy makers, managers and clinicians worldwide.

Frail older people with chronic and complex health conditions have high re-admission rates with approximately 25% of older people being readmitted within three months of hospital discharge [31]. Continuity and integration of care following discharge from the acute setting is consistently recommended but difficult to achieve given the current divide between funding for acute and primary care settings. The FORTRESS study aims to work across settings to address frailty identified in a hospital environment. Evidence for cost-effectiveness of preventive, integrated care is generally limited due to a wide variety in study populations, interventions and evaluations [32]. However, previous studies have demonstrated that a multicomponent interdisciplinary frailty intervention is both more effective and less costly than usual care [24]. The FORTRESS study aims to demonstrate that the cost of delivering the intervention will be significantly outweighed by the cost of hospital re-admissions.

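### Confidence intervals are promised around ICERs that the trial expects to be negative, and negative ratios have no usable order

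*Protocol article*

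**What the plan says.** The Economic analysis section of the protocol article defines three ratios: "cost per extra person avoiding readmission, cost per extra person avoiding frailty, and cost per quality adjusted life years (QALY) gained". It then states that "Bootstrapping will be used to estimate a distribution around costs and health outcomes", and that the bootstrap will also serve "to calculate the confidence intervals around the incremental cost-effectiveness ratios". No condition is attached to these intervals, and the type of bootstrap interval is not named.

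The same section plans two displays of joint uncertainty: "results will be plotted on a cost-effectiveness plane" and, after a probabilistic sensitivity analysis, "a cost-effectiveness acceptability curve (CEAC) will be plotted".

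On the expected direction, the Discussion says "The FORTRESS study aims to demonstrate that the cost of delivering the intervention will be significantly outweighed by the cost of hospital re-admissions" and cites earlier work in which a "multicomponent interdisciplinary frailty intervention is both more effective and less costly than usual care". The Sample size section plans on a mean of 35 against 50 readmission days.

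**The concern.** An ICER interval can be read as a range from more to less favourable only where a larger ratio is consistently worse or consistently better. That holds when all replicates lie in one trade-off quadrant (dearer and better, or cheaper and worse). The trial is aiming at the cheaper-and-better quadrant, where it fails for two reasons.

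- A negative ratio arises both when the intervention is cheaper and better and when it is dearer and worse. The sign does not tell them apart.
- Even within the cheaper-and-better quadrant, the size of the ratio does not track how good the result is.

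If the health difference is also close to zero relative to its standard error, some replicates divide by values near zero on either side, and the ranked ratios spread without useful limit. At stake is whether the stated uncertainty for cost-effectiveness can be interpreted, including when the underlying result is favourable.

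**Working it through.** The plan states no figure that depends on this interval, so there is nothing to reproduce. The documents give no standard errors for cost or effect. All cost and effect inputs below are assumptions, shown over a range.

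**1. Ordering of negative ratios.** ICER = cost difference / effect difference. Net monetary benefit (NMB) = threshold × effect difference − cost difference, with an assumed threshold of 50,000.

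| Cost difference | Effect difference | ICER | NMB |
|---|---|---|---|
| −1,000 | +0.05 | −20,000 | 2,500 + 1,000 = 3,500 |
| +1,000 | −0.05 | −20,000 | −2,500 − 1,000 = −3,500 |
| −1,000 | +0.10 | −10,000 | 5,000 + 1,000 = 6,000 |

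Rows 1 and 2 share a ratio but call for opposite decisions. Rows 1 and 3 have the same saving. Row 3 has twice the gain, yet its ratio is less negative. NMB orders all three correctly.

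**2. Spread over quadrants.** Cost and effect differences were drawn as independent normals, with standard error 2,500 for cost and 0.02 for QALYs. The mean differences were varied:

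- Weak on both: cost −1,000 (z = −0.4), QALY +0.02 (z = 1).
- Clear saving, uncertain gain: cost −5,000 (z = −2), QALY +0.02 (z = 1).
- Strong on both: cost −7,000 (z = −2.8), QALY +0.056 (z = 2.8). For scale, 2.8 = 1.96 + 0.84 is the expected z at the planned 80% power and two-sided 5% level, if cost followed readmission days and intervention cost were ignored.

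Under independence the quadrant shares are products of normal probabilities. For the weak case: cheaper and better 0.655 × 0.841 = 0.55; dearer and better 0.345 × 0.841 = 0.29; cheaper and worse 0.655 × 0.159 = 0.10; dearer and worse 0.345 × 0.159 = 0.05.

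The standard error of NMB is √((50,000 × 0.02)² + 2,500²) = √(1,000² + 2,500²) = 2,693, so its 95% interval is the mean ± 1.96 × 2,693 = mean ± 5,277. The ICER limits are the simulated 2.5th and 97.5th percentiles.

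| Case | Cheaper and better | ICER, ranked 95% limits | Mean NMB | NMB 95% interval |
|---|---|---|---|---|
| Weak on both | 55% | about −1.08 to +0.99 million | 2,000 | −3,277 to 7,277 |
| Clear saving, uncertain gain | 82% | about −2.6 to +2.3 million | 6,000 | 723 to 11,277 |
| Strong on both | 99.5% | about −437,000 to −32,000 | 9,800 | 4,523 to 15,077 |

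In the middle case NMB lies wholly above zero, while the ranked ICER interval covers millions in both directions. In the strong case the ICER interval is bounded, but by step 1 neither end is the favourable one. A correlation of −0.3 between cost and effect leaves this pattern unchanged.

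**3. How likely crossing is.** Over assumed cost z from −2.8 to 0 and effect z from 0.5 to 2.8 (correlation −0.3), the probability that the 95% interval on at least one axis includes zero runs from 0.34 to 0.99. It is 0.55 or more in every combination except the strongest.

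**The case against.** Four points can be made for the plan.

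- **The method is not specified.** The article does not say that ratios will be ranked. Quadrant-aware intervals, such as ordering replicates by angle on the plane, can be built from the same joint distribution, and a fuller economic plan may say so. This stands in part: the figures above apply to an interval formed by ranking ratios. What the article does state is an unconditional interval around each ratio, and the lack of order among negative ratios belongs to the ratio itself.
- **The plane and acceptability curve are already planned.** Both remain readable across quadrants, and the curve gives the probability of positive net benefit over a range of thresholds. This stands and is why the point is minor. It does not make the promised interval interpretable.
- **A hoped-for saving does not scatter replicates.** A reader might infer from the aim that "the cost of delivering the intervention will be significantly outweighed by the cost of hospital re-admissions" that replicates must fall in several quadrants. The documents do not support that. A clear saving with a clear gain puts 99.5% in one quadrant; scatter comes from imprecision. What the expected saving brings is the ordering problem.
- **The ICER interval is not declared the main economic result.** A reader might take it as such, but nothing in the section ranks it above the plane or the curve.

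**Conclusion.** The point holds in a limited form. The article commits without condition to confidence intervals around three ICERs, in a trial whose own expectation is lower cost with better outcomes. There the ratio is negative and cannot be ordered, even when nearly every replicate lies in one quadrant. If cost or effect is imprecise, an interval from ranked ratios is uninterpretable as well.

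The ordering problem is arithmetic and needs no assumption. The quadrant shares (99.5% down to 55% cheaper and better) and the interval widths rest on assumed differences, standard errors and normality, and on ranking as the interval method. They illustrate a range and do not forecast this trial. The consequence is minor and confined to the economic evaluation. The primary outcome, sample size and significance level are unaffected.

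**What to change.** Keep the ICER as a point estimate with the planned plane and acceptability curve. Replace the ICER confidence interval with bootstrap intervals for incremental cost, incremental effect and, for QALYs, incremental net monetary benefit at a stated threshold or range of thresholds.

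For readmission and frailty the documents give no threshold. There, report intervals for incremental cost and incremental effect with the share of replicates in each quadrant, or net benefit over a range of values.

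The cost is a sentence or two in the economic plan. The same bootstrap output serves, with no extra data. The one downside is that a QALY threshold or range has to be named in advance.
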